## Abstract

**Background:**

Vietnam and Saudi Arabia have high disease burden of primary hepatocellular carcinoma (HCC). Early detection in asymptomatic patients at risk for HCC is a strategy to improve survival outcomes in HCC management. GALAD score, a serum-based panel, has demonstrated promising clinical utility in HCC management. However, in order to ascertain its potential role in the surveillance of the early detection of HCC, GALAD needs to be validated prospectively for clinical surveillance of HCC (i.e., phase IV biomarker validation study). Thus, we propose to conduct a phase IV biomarker validation study to prospectively survey a cohort of patients with advanced fibrosis or compensated cirrhosis, irrespective of etiologies, using semi-annual abdominal ultrasound and GALAD score for five years.

**Methods:**

We plan to recruit a cohort of 1,600 patients, male or female, with advanced fibrosis or cirrhosis (i.e., F3 or F4) and MELD ≤ 15, in Vietnam and Saudi Arabia (*n* = 800 each). Individuals with a liver mass ≥ 1 cm in diameter, elevated alpha-fetoprotein (AFP) (≥ 9 ng/mL), and/or elevated GALAD score (≥ -0.63) will be scanned with dynamic contrast-enhanced magnetic resonance imaging (MRI), and a diagnosis of HCC will be made by Liver Imaging Reporting and Data System (LiRADS) assessment (LiRADS-5). Additionally, those who do not exhibit abnormal imaging findings, elevated AFP titer, and/or elevated GALAD score will obtain a dynamic contrast-enhanced MRI annually for five years to assess for HCC. Only MRI nearest to the time of GALAD score measurement, ultrasound and/or AFP evaluation will be included in the diagnostic validation analysis. MRI will be replaced with an abdominal computed tomography scan when MRI results are poor due to patient conditions such as movement etc. Gadolinium-ethoxybenzyl-diethylenetriamine pentaacetic acid-enhanced MRI will not be carried out in study sites in both countries. Bootstrap resampling technique will be used to account for repeated measures to estimate standard errors and confidence intervals. Additionally, we will use the Cox proportional hazards regression model with covariates tailored to the hypothesis under investigation for time-to-HCC data as predicted by time-varying biomarker data.

**Discussion:**

The present work will evaluate the performance of GALAD score in early detection of liver cancer. Furthermore, by leveraging the prospective cohort, we will establish a biorepository of longitudinally collected biospecimens from patients with advanced fibrosis or cirrhosis to be used as a reference set for future research in early detection of HCC in the two countries.

**Trial registration:**

Name of the registry: ClinicalTrials.gov

Registration date: 22 April 2022

Trial registration number: NCT05342350

URL of trial registry record

## Background

Vietnam and Saudi Arabia have some of the highest disease burdens of primary hepatocellular carcinoma (HCC) in the world [1]. More than 80% of HCC cases develop on the background of advanced fibrosis or cirrhosis [2]. Up to 90% of advanced fibrosis/cirrhosis cases, hence high risk for HCC, are due to hepatitis B virus (HBV), hepatitis C virus (HCV) and/or non-alcoholic steatohepatitis (NASH) in Vietnam or Saudi Arabia. The incidence of HCC in patients with HBV or HCV and/or NASH-associated advanced fibrosis is as high as 4% per year [3, 4], for cirrhosis 8% per year [2], making HBV-HCV or NASH in the presence of significant fibrosis the most significant risk factor for HCC development. Furthermore, up to 70% of newly diagnosed HCC cases in Vietnam and Saudi Arabia are at an advanced symptomatic stage, e.g., with Barcelona Clinic Liver Cancer staging system (BCLC)-C or D [5, 6]. Likewise, recent publications in Vietnam and Saudi Arabia documented that 80–92% of patients with HCC presented symptomatically [6, 7]. These data indicate that most patients with HCC in Vietnam or Saudi Arabia seek medical attention too late in their disease course; thus, therapeutic interventions are suboptimal at diagnosis.

Early detection in asymptomatic patients is a strategy to improve survival outcomes in HCC management. GALAD score is a serum biomarker-based panel that can improve early HCC detection in patients with chronic liver disease, including liver fibrosis and cirrhosis. In this protocol, GALAD will combine gender and age with the results from alpha-fetoprotein (AFP), lens culinaris agglutinin (LCA) bound fraction of AFP (AFP-L3%), and protein induced by vitamin K absence-II (PIVKA-II) or des-gamma-carboxy-prothrombin (DCP) levels. This score has been internally and externally validated [8] and recently received breakthrough designation from the United States Food and Drug Administration (US FDA). The performance of GALAD has been evaluated as a surveillance test for HCC in the United States, United Kingdom, Germany, Japan, and Hong Kong in case–control studies as well as in studies with design as PROBE (prospective specimen collection and retrospective blinded evaluation) [9]. However, it has not yet been evaluated in Vietnam or Saudi Arabia [8]. And most importantly, GALAD has not been investigated and validated prospectively for clinical surveillance of HCC in which GALAD score is applied to individuals in real-time and diagnostic procedures are performed for those with an elevated GALAD test (≥ -0.63).

In order to provide robust data for the potential use of GALAD in Vietnam and Saudi and as the next step in GALAD score biomarker development [10], we propose to conduct a phase IV biomarker validation study to prospectively survey a cohort of patients at risk for HCC (i.e., patients with advanced fibrosis or compensated cirrhosis and irrespective of cirrhosis etiologies), using semi-annual abdominal ultrasound and GALAD Score for five years. In doing so, we aim to validate the potential role of GALAD Score for clinical surveillance and early detection of HCC in Vietnam and Saudi Arabia. Additionally, we will collect and archive biospecimens to promote future research in chronic liver disease in Vietnam and Saudi Arabia.

## Methods / design

### Objectives

The primary objective of the study is to prospectively evaluate the performance of GALAD score as a biomarker-based surveillance model to detect early HCC in patients with advanced fibrosis or cirrhosis (e.g., Metavir F3 or higher, with model for end-stage liver disease [MELD] 15 or lower). The secondary objective is to collect and archive biospecimens to develop a bio-repository for future studies in chronic liver diseases.

### Outcome measures

The primary endpoint is the performance of GALAD score determined in association with HCC detection by LiRADS criteria in a cohort with advanced fibrosis or cirrhosis (e.g., Metavir F3 or higher, with MELD 15 or lower) undergoing prospective surveillance every six months for five years. Performance of GALAD score will be determined by using the GALAD score cut-off value of -0.63 to prospectively survey a cohort of 1,600 patients with advanced fibrosis and early cirrhosis (e.g., Metavir F3 or higher, with MELD 15 or lower) for early detection of HCC by Liver Imaging Reporting and Data System (LiRADS) assessment (LiRADS-5). The GALAD cut-off value was previously determined in case–control studies [11]. For the establishment of the biorepository, the endpoint is the proportion of study participants who agree to consent for bio-specimen when invited.

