### Study population

We plan to recruit a cohort of 1,600 patients, male or female, with advanced fibrosis/cirrhosis F3 or F4, and MELD ≤ 15, in Vietnam (*n* = 800) and Saudi Arabia (*n* = 800).

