### Eligibility criteria

An individual must meet all the following criteria for inclusion in the study:Adults aged 18 or olderAll genders and ethnicitiesDiagnosis of fibrosis and cirrhosis based on histology and/or image showing cirrhotic liver with splenomegaly and platelet counts < 120 mm^3^, or esophageal or gastric varices on endoscopy AND presence of chronic liver disease/Fibroscan and/or Fib-4 and/or aspartate aminotransferase (AST) to platelet ratio index (APRI)/ acoustic radiation force impulse (ARFI). For viral hepatitis: transient elastography (TE) ≥ 9 kPa, APRI ≥ 1; for non-alcoholic fatty liver disease (NAFLD)/NASH: TE > 8 kPa, FIB-4 > 1.3Individuals already confirmed having cirrhosis with MELD ≤ 15 from any etiology (chronic HBV, chronic HCV, NASH, cirrhosis, etc.)No significant hepatic decompensationNo hepatorenal syndromeFor chronic HBV and/or HCV carrier, with or without treatmentNo prior or current treatment for HCCNo cancer history within five yearsNo participation in a trial for HCC treatmentNo prior solid organ transplantAlbumin, bilirubin, creatinine, and international normalized ratio (INR) labs within the past 30 daysAFP labs within 180 days irrespective of AFP titerImaging showing no HCC within 180 daysFor other medical historyNo known AIDS-related diseasesNo significant co-morbid conditions with life expectancy < 5 yearsNo other cancer(s)Agree to the collection of biosamples (serum, plasma, and urine) at each of the six months follow-ups during the study durationProvision of signed and dated informed consent formStated willingness to comply with all study procedures and availability for the duration of the study and up to five years post-study follow upWillingness to give written informed consent to be enrolled in the databaseResides in Vietnam or Saudi Arabia at the time of study and provides contact information (email and/or cell phone number for texting)Two phone numbers and personal identification numbers (citizen identification number)

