**Fig. 2 Fig2:**
[figure not shown]
Study Schema. Patients with chronic liver diseases from hospital database of the participating sites will be screened and invited for enrollment if eligible. Next, we prospectively survey the eligible cohort of patients at risk for HCC (i.e. patients with advanced fibrosis or compensated cirrhosis and irrespective of cirrhosis etiologies), using semi-annual abdominal ultrasound and GALAD Score for five years. During the 5-year follow-up, individuals with a liver mass ≥ 1 cm in diameter and/or elevated GALAD score (≥ -0.63) will be scanned with dynamic contrast-enhanced MR,I and a diagnosis of HCC will be made by LiRADS assessment (LiRADS-5). Additionally, those who do not exhibit abnormal imaging findings and/or elevated GALAD score will obtain a dynamic contrast-enhanced MRI annually for five years to assess for HCC

During the 5-year time frame, we anticipate at least 80 (approximately 16 each year if 1% incidence x five years for both cohorts in Vietnam and Saudi Arabia) or as many as 320 (64 per year if 4% incidence x five years for both cohorts in Vietnam and Saudi Arabia) incident HCC cases given the high HCC incidence rate in Vietnam and Saudi Arabia. With the range of 80 to 320 anticipated HCC cases, we will have 90% to 99% power, respectively, to detect a meaningful difference in the cases vs. control (more on sample size calculation below). We will compare sensitivity for early HCC detection (primary outcome measures), false-positive results, and resultant diagnostic evaluation.

By leveraging the prospective cohort, we will establish a biorepository of longitudinally collected biospecimens from patients with fibrosis/cirrhosis to be used as a reference set for future research. Clinical, laboratory, and imaging data, urine, and plasma biospecimens are from participants for up to five years; data are collected only from participants who maintain the absence of evidence of HCC on imaging and/or biopsy. Biospecimens and associated de-identified clinical data from participants enrolled in this study will be stored in Vietnam for participants from Vietnam and in Saudi Arabia for participants enrolled from Saudi Arabia.

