### Enrollment

The participant is considered enrolled in the study once the consent is signed and the Registration Form has been completed. Activities at the initial screening and or study registration visit include:Sign the formsSignature on the study consent and biorepository consent formSignature on the Health Insurance Portability and Accountability Act (HIPAA) authorization form for the studyAssignment of the study participant identification numberMedical and medication historyPhysical examination including vital signs, height, weight, anthropometric measurements, handgrip strength measurementScreening electrocardiogram (ECG)Acanthosis nigricans and liver signsObtaining laboratory and other information (on the co-variates list)Instructing participant to bring to initial screening visit his/her health history information or related materialsParticipant to sign medical records release to obtain study labs and imagingParticipant to provide location and contact informationCoordinator to register participants on clinic data systemCoordinator to request prior reports and study imaging/procedures from healthcare providerLaboratory testHematology (complete blood count)Chemistry (hepatic panel, hemoglobin A1c (HbA1c), fasting lipid profile and fasting glucose and insulin levels, fasting blood (plasma) for specimen bankingImaging diagnostic: abdominal ultrasound, Fibroscan, or ARFILiver biopsy (if needed)Provision of the standard of care educational materials (delay providing these to the participant until confirmed eligible for the study)Schedule for the second visit

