### Schedule of activities

Data will be collected during screening (initial visit) and at semi-annual intervals thereafter (a maximum of ten visits). Schedule of activities (Table 1) displays the data collection schedule for screening and follow-up.

**Table 1 Tab1:** Schedule of activities

Procedures	Screening/baseline (Visit 1)	Study Visit 2	Study Visit 3	Study Visit 4	Study Visit 5	Study Visit 6	Study Visit 7	Study Visit 8	Study Visit 9	Final Study Visit 10
Informed consent	X									
Demographics	X									
Home address/Phone number	X	X	X	X	X	X	X	X	X	X
Medical history	X	X	X	X	X	X	X	X	X	X
Collect and archive serum (15 mL blood, 50 mL urine)	X	X	X	X	X	X	X	X	X	X
Concomitant medication review	X	X	X	X	X	X	X	X	X	X
Physical exam (including height and weight)	X	X	X	X	X	X	X	X	X	X
Vital signs	X	X	X	X	X	X	X	X	X	X
Height	X									
Weight	X	X	X	X	X	X	X	X	X	X
Waist circumference	X	X	X	X	X	X	X	X	X	X
Performance status	X	X	X	X	X	X	X	X	X	X
Handgrip strength measurements	X	X	X	X	X	X	X	X	X	X
Hematology	X	X	X	X	X	X	X	X	X	X
Serum chemistry	X	X	X	X	X	X	X	X	X	X
Adverse event review and evaluation		X	X	X	X	X	X	X	X	X
Radiologic/Imaging assessment (Abdominal Ultrasound and/or cross section imaging if triggered)	X	X	X	X	X	X	X	X	X	X
Dynamic contrast-enhanced CT or MRI	X		X		X		X			X
Fibroscan	X									X
Complete Case Report Forms (CRFs) that have clinical data and events	X	X	X	X	X	X	X	X	X	X

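### Read literally, the biorepository endpoint is fixed at or near 100%, because agreeing to biosamples is a condition of entry and the denominator is not defined otherwise

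*Protocol article*

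**What the plan says.** The Protocol article, Objectives, gives one secondary objective: "The secondary objective is to collect and archive biospecimens to develop a bio-repository for future studies in chronic liver diseases". The Outcome measures section attaches one endpoint to it: "the endpoint is the proportion of study participants who agree to consent for bio-specimen when invited". No target, expected value or precision is given.

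Four other places bear on who can be counted:

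- **Eligibility criteria.** The list opens with "An individual must meet all the following criteria for inclusion in the study", and one item is "Agree to the collection of biosamples (serum, plasma, and urine) at each of the six months follow-ups during the study" (the sentence continues to the end of the study period). A patient who refuses to sign the informed consent form is also excluded.
- **Enrollment.** "The participant is considered enrolled in the study once the consent is signed and the Registration Form has been completed". Signing the biorepository consent form is listed with the study consent among the activities of the screening or registration visit, with no note that it is optional.
- **Schedule of activities, Table 1.** The row "Collect and archive serum (15 mL blood, 50 mL urine") is marked at all ten visits, with no opt-out shown.
- **Fig. 2 caption.** Patients from the hospital databases "will be screened and invited for enrollment if eligible".

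**The concern.** An endpoint has to be able to take more than one value. Here the numerator is those who agree to give specimens, and the denominator, as worded, is study participants. If nobody becomes a study participant without agreeing, the two are the same people.

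This is the only endpoint stated for the secondary objective. A literal 100% would not measure acceptability of banking, because refusers have been screened out. Nor would it measure how complete the repository is, because agreement at invitation does not change when later samples are missed. Readers could still take the figure as evidence of universal acceptance. If refusals are not recorded during recruitment, an analysis plan written later could not easily recover the denominator.

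**Working it through.** The plan gives no figure for this endpoint, so there is none to reproduce. The check sets the definition against the entry rules under each reading that the text allows.

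**Inputs.** Planned cohort: "We plan to recruit a cohort of 1,600 patients" (Study population). Visits per participant: up to ten (Schedule of activities). Allowance for missing data or loss to follow-up: up to 30% (Missing data). Refusal rates are not in the document; 5%, 10%, 20% and 30% are assumed for illustration.

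**Reading A: the denominator is enrolled participants, and agreement to biosamples covers banking.**
- Endpoint = agreeing participants / enrolled participants = 1,600/1,600 = 100%.
- Exact (Clopper-Pearson) two-sided 95% lower limit when all agree: 0.025^(1/n) = 0.025^(1/1600) = 99.77%.
- The interval looks precise, but it reflects the entry rule and not patients' willingness.

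**Reading B: the denominator is all otherwise eligible patients invited.** Endpoint = 1 − r, where r is the refusal rate. If refusal of banking were the only reason for not enrolling, the number invited to reach 1,600 would be 1,600/(1 − r).

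| Assumed refusal r | Invited | Refusers | Endpoint, reading B | Endpoint, reading A |
|---|---|---|---|---|
| 5% | 1,684 | 84 | 95% | 100% |
| 10% | 1,778 | 178 | 90% | 100% |
| 20% | 2,000 | 400 | 80% | 100% |
| 30% | 2,286 | 686 | 70% | 100% |

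Reading B responds to refusal; reading A does not.

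**Reading C: collection is compulsory but consent to banking is optional.** Endpoint = participants who sign the biorepository form / 1,600. This could fall below 100%. But the Enrollment section does not call the signature optional, and Table 1 archives specimens for everyone.

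**After enrollment.** The ceiling on scheduled specimen visits is 1,600 × 10 = 16,000; the true number is lower because participants leave the study on developing HCC. As an illustration only, suppose the plan's 30% allowance applied to specimen visits. Then 0.70 × 16,000 = 11,200 would be banked, which is 70% completeness. Reading A would still report 100%, because it counts agreement and not specimens.

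**The case against.** The strongest reply is that the text does not force reading A. Three parts of it have weight.

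1. The endpoint sentence ends with a reference to invitation, and the article uses the word participant for people not yet enrolled. The Fig. 3 caption speaks of a participant who, if agreeable, may then enter the enrollment phase, and the Enrollment section describes a participant becoming enrolled. So the sponsor may well have meant agreement among those invited. This stands as a plausible intention. It does not settle the matter, because no denominator of invited patients is stated.
2. It is tempting to add that the endpoint is also 100% among invited patients, since agreement is part of eligibility and only eligible patients are invited. That does not follow. Agreement cannot be known before the invitation, and the Fig. 3 caption introduces the study first and asks for agreement afterwards.
3. The inclusion criterion requires agreement to collection and does not mention archiving for future research. Enrollment is conditioned on the consent and the Registration Form, and nothing says that a patient who declines the biorepository form is turned away. This is also fair. Against it, the biorepository signature carries no optional label and archiving is scheduled for all.

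The reply also notes that this is a descriptive process measure with no hypothesis or power claim, and that a condensed article may leave fine detail to the full protocol. That limits the weight of the point. But the endpoint and the criterion are both stated here, and taken at their word they collide.

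**Conclusion.** The point holds in a limited form. On the literal wording, the only secondary endpoint is fixed at or near 100% and cannot inform its objective. It becomes informative only under reading B or reading C, and the document states neither.

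A reader might infer the stronger claim that the endpoint is 100% by design on any reading. The document does not support that: the reference to invitation, the loose use of participant and the gap between collection and banking each leave room for a value below 100%.

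The size depends on refusal, for which the document gives no figure. Under the assumed rates, the literal reading would overstate acceptance by 5 to 30 percentage points. The conclusion that the denominator needs defining does not depend on those rates. The primary endpoint and the sample size, which rests on HCC incidence, are untouched. The change should be made, but it is not critical to the trial's main question.

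**What to change.** In Outcome measures, do one of the following:

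- define the denominator as all otherwise eligible patients who are invited, and record each patient's agreement to or refusal of banking at screening; or
- state that consent to banking is optional and separate from collection, and reconcile the Eligibility criteria, the Enrollment activities and Table 1 with that.

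In either case, also report a measure that can vary after enrollment, such as the proportion of scheduled visits (up to ten per participant) with serum, plasma and urine banked.

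The cost is a line or two of wording, one item recorded at screening, and a visit-level specimen record. The article describes neither a screening log nor visit-level specimen tracking, so these may be new, though small, tasks for the sites. Refusals should be recorded from the start of recruitment or as soon as possible, because they are hard to reconstruct afterwards.

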### Study design

This will be a prospective observational cohort phase IV biomarker validation study using semi-annual abdominal ultrasound and GALAD score.

### Study population

We plan to recruit a cohort of 1,600 patients, male or female, with advanced fibrosis/cirrhosis F3 or F4, and MELD ≤ 15, in Vietnam (*n* = 800) and Saudi Arabia (*n* = 800).

### Eligibility criteria

An individual must meet all the following criteria for inclusion in the study:Adults aged 18 or olderAll genders and ethnicitiesDiagnosis of fibrosis and cirrhosis based on histology and/or image showing cirrhotic liver with splenomegaly and platelet counts < 120 mm^3^, or esophageal or gastric varices on endoscopy AND presence of chronic liver disease/Fibroscan and/or Fib-4 and/or aspartate aminotransferase (AST) to platelet ratio index (APRI)/ acoustic radiation force impulse (ARFI). For viral hepatitis: transient elastography (TE) ≥ 9 kPa, APRI ≥ 1; for non-alcoholic fatty liver disease (NAFLD)/NASH: TE > 8 kPa, FIB-4 > 1.3Individuals already confirmed having cirrhosis with MELD ≤ 15 from any etiology (chronic HBV, chronic HCV, NASH, cirrhosis, etc.)No significant hepatic decompensationNo hepatorenal syndromeFor chronic HBV and/or HCV carrier, with or without treatmentNo prior or current treatment for HCCNo cancer history within five yearsNo participation in a trial for HCC treatmentNo prior solid organ transplantAlbumin, bilirubin, creatinine, and international normalized ratio (INR) labs within the past 30 daysAFP labs within 180 days irrespective of AFP titerImaging showing no HCC within 180 daysFor other medical historyNo known AIDS-related diseasesNo significant co-morbid conditions with life expectancy < 5 yearsNo other cancer(s)Agree to the collection of biosamples (serum, plasma, and urine) at each of the six months follow-ups during the study durationProvision of signed and dated informed consent formStated willingness to comply with all study procedures and availability for the duration of the study and up to five years post-study follow upWillingness to give written informed consent to be enrolled in the databaseResides in Vietnam or Saudi Arabia at the time of study and provides contact information (email and/or cell phone number for texting)Two phone numbers and personal identification numbers (citizen identification number)

A patient who meets any of the following criteria will be excluded from participation in this study:Decompensated cirrhosis (variceal bleeding, hepatic encephalopathy, ascites, spontaneous bacterial peritonitis, and/or hepatorenal syndrome) or MELD > 15Individuals who already have HCC, with or without HCC treatmentOn liver transplantation list or anticipated to be on the liver transplantation list during the study durationAny serious or active medical or psychiatric illness that, in the opinion of the investigator, would interfere with patient treatment, assessment, or compliance with the protocolKnown HIV positive statusTaking Vitamin K within seven days prior to clinic follow or having disease affecting Vitamin K levels.Active drug use or dependence that, in the opinion of the study investigator, would interfere with adherence to study requirementsInadequate documentationIndividuals who cannot, do not want to, or refuse to sign the informed consent form

